#### Study population and recruitment site

3.1.1.

We aim to recruit 900 pregnant individuals from Denver Health obstetrics clinics. Pregnant individuals (18 years or older) who are English or Spanish speaking and at less than 30 gestational weeks are eligible. Individuals at 30 or more gestational weeks are excluded due to insufficient time to complete ROSE prior to delivery. The target sample size was determined based on power analyses accounting for an estimated 20 % attrition rate (10 % during pregnancy and an additional 10 % postpartum) and our primary analyses testing inferiority of virtual to in-person La Luz (see below).

Denver Health is a Federally Qualified Health Center serving low resourced and underserved pregnant individuals. The obstetrics clinics at Denver Health serve individuals from the surrounding urban metropolitan Denver area. Denver is a racially and ethnically diverse city, which is reflected in the Denver Health patient population. Among all patients who received care from Denver Health in 2023, 49 % identify as Hispanic/Latine, 13 % Black or African American, 30 % non-Hispanic White, and 4 % Asian or Pacific Islander [54]. Spanish-speaking patients make up a substantial portion of the Denver Health patient population, and some patients speak only Spanish [55].

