### Baseline study visit and randomization

3.2.

At their baseline study visit, participants complete informed consent with research staff and the baseline survey via REDCap over the phone or via Zoom videoconferencing. At the end of their baseline visit, participants are randomly assigned to one of the two conditions (virtual or in-person) using a secure and locked computer program and are scheduled for their first group session. Research staff are blind to participants’ condition assignment during survey administration and data analysis.

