##### Secondary outcome.

Secondary analyses will involve evaluating depression assessed via the Edinburgh Postnatal Depression Scale (EPDS), which is widely used for screening maternal depression across the perinatal period [63]. Participants provide ratings on a 4-point scale on symptoms over the past week. Final sum scores range from 0 to 30, with higher scores indicating greater levels of depression. Previous studies support both good internal consistency (α > 0.80) and validity of the EPDS [64]. The EPDS has been validated among Spanish-speaking mothers [65]. The EPDS is standardly administered at the prenatal and postpartum medical visits at Denver Health. We collect EPDS scores from participants’ electronic health records to address real-world feasibility and sustainability of depression monitoring.

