#### Analysis testing inferiority of virtual vs. in-person La Luz

3.6.1.

Primary analyses will use intent-to-treat design to evaluate the effectiveness of the intervention among all enrolled participants [66]. To test whether virtual La Luz will yield a similar benefit (i.e., is non-inferior) as in-person La Luz for perinatal depression, multilevel models (timepoints nested within participants) including random intercepts and slopes will be used. Multilevel modeling accounts for nested data structure and is robust to missing data [67]. In line with non-inferiority testing, we will use a one-sided test and statistical significance set at *p* < .05 with margin of non-inferiority set to an effect size Cohen’s *d* of 0.25 for our estimate contrasts of total change in our multilevel model. Model-based total change estimate will provide us flexibility if the change over time is nonlinear (i.e., log-linear, parabolic, piecewise, etc.). A negative effect size would indicate more reduction for virtual compared to in-person, whereas, a positive effect size would indicate more reduction for in-person compared to virtual. Non-inferiority will be shown if the effect size for contrast of total change yields a one-sided 95 % upper bound smaller than *d* = +0.25. If the one-sided 95 % upper bound is bigger than *d* = +0.25, the confidence interval for the true effect size of the contrast of total change does not lie totally within the non-inferior region, and non-inferiority cannot be concluded (illustrated in Fig. 2 with ±*d* as the indicated margins). Given that intent-to-treat approaches can bias non-inferiority trials toward finding the interventions to be non-inferior, we will also conduct a sensitivity analysis including only participants who complete the intervention [68,69]. Secondary analyses will follow the same analytic procedures but with EPDS scores collected from electronic health records as the outcome.

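### The primary multilevel model is called robust to missing outcomes without condition; it is valid only under missing at random, and the one named sensitivity analysis does not test that

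*Protocol article*

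**What the plan says.** The missing-data position is one sentence in section 3.6.1: "Multilevel modeling accounts for nested data structure and is robust to missing data". The same section makes intent-to-treat on all enrolled participants the primary analysis, using random intercepts and slopes. It specifies a "one-sided test and statistical significance set at *p* < .05 with margin of non-inferiority" set at an effect size "of 0.25 for our estimate contrasts of total change in our multilevel model". It names one sensitivity analysis, restricted to participants who complete the intervention. The stated reason is that intent-to-treat can lean towards non-inferiority; missing outcomes are not mentioned.

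Section 3.1.1 gives the target and the expected loss: "We aim to recruit 900 pregnant individuals from Denver Health obstetrics clinics", the power analyses "accounting for an estimated 20 % attrition rate (10 % during pregnancy and an additional 10 % postpartum". Loss is not split by arm.

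Section 3.5.2 adds a source that does not depend on answering study surveys: "We collect EPDS scores from participants’ electronic health records". Section 3.6.1 analyses these scores as a secondary outcome by the same procedures.

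**The concern.** A likelihood-based mixed model uses every available timepoint, and its estimates are valid if missingness depends only on observed data and the model is right. It then in effect predicts each non-responder's later course from that person's observed scores and from others in the same arm. If people stop answering because of current mood that was not recorded, the prediction is wrong and nothing in the fit shows it. Presenting robustness as a property of the method turns an untestable assumption into a settled fact.

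This matters more here than in a superiority trial. A positive effect size favours in-person delivery, and the claim rests on the upper bound staying below +0.25. If virtual-arm non-responders are worse than modelled by more than in-person non-responders are, the estimate falls and the bound moves towards the claim.

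The completer analysis does not fill the gap. The four group sessions take place before birth, whereas surveys run to 12 months postpartum. A completer can still miss later surveys, and a non-completer can answer them all. The restricted analysis selects on an event after randomisation and still assumes missing at random for the surveys that its members miss.

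**Working it through.** **Inputs from the protocol article.** N = 900 and 20% attrition (section 3.1.1); one-sided 0.05 and margin d = 0.25 (section 3.6.1); two randomised arms (section 3.2).

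**Assumptions.** Allocation 1:1 (the ratio is not stated); SD = 1, so that d is in SD units; attrition equal by arm unless stated; a simple two-sample standard error. The model-based contrast of total change will have a different standard error, so the results are illustrative.

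**The plan's own figure.** No power is stated, so 900 cannot be reproduced. It can be placed: the total for margin 0.25, true difference 0 and one-sided 0.05, divided by 0.80, is
- 80% power: 396/0.80 = 495
- 90% power: 550/0.80 = 688
- 95% power: 694/0.80 = 868
- 96% power: 738/0.80 = 923

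With 900 × 0.80 = 720, or 360 per arm, SE = √(2/360) = 0.0745 and power = Φ(0.25/0.0745 − 1.645) = 95.6%. The sample size is not shown to be wrong. The issue is bias, not power.

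**Hidden shift.** Let m be the share missing per arm and δ the amount, in SD, by which virtual-arm dropouts are worse than modelled over and above in-person dropouts. The contrast is then too favourable by b = m × δ.

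**Error at the margin.** If the true difference is 0.25, P(false non-inferiority) = Φ(b/0.0745 − 1.645). With m = 0.20:

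| δ (SD) | b | Error |
|---|---|---|
| 0 | 0 | 5.0% |
| 0.10 | 0.02 | 8.4% |
| 0.25 | 0.05 | 16.5% |
| 0.50 | 0.10 | 38.1% |
| −0.25 | −0.05 | 1.0% |
| −0.50 | −0.10 | 0.1% |

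The shifts of 0.05 and 0.10 are 20% and 40% of the margin.

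**Unequal attrition.** If dropouts in both arms are 0.5 SD worse than modelled, 25% virtual against 15% in-person attrition gives b = (0.25 − 0.15) × 0.5 = 0.05 and an error of 16.5%. Reversed, b = −0.05 and the error is 1.0%. With equal attrition and equal departures, b = 0 and the error stays at 5%.

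**Tipping point with an observed difference of 0.** Upper bound = 1.645 × 0.0745 = 0.1226. Room to the margin = 0.25 − 0.1226 = 0.1274. Non-inferiority is lost at δ = 0.1274/0.20 = 0.64 SD. With the same SE it is 1.27 SD at 10% missing and 0.42 SD at 30%.

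**The case against.** The strongest reply is that this is a condensed article whose statistical analysis plan is not shown. Assumptions about the missingness mechanism and tipping-point analyses are often left there, and a multilevel model on all available timepoints is a standard choice. This stands as far as it goes: silence on such analyses is not an error, and no other primary model is needed. It does not cover a sentence that states the property without its condition.

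Four stronger readings are tempting, and the document does not support them.
- A reader might infer that no planned analysis could expose the problem. The EPDS analysis could do so in part, because those scores come from routine visits and may exist for people who stop answering surveys. It is only indirect: it is a separate outcome, has its own missingness, and is not linked to survey dropout.
- A reader might infer that the completer analysis was offered as a missing-data check and fails as one. It was offered as a guard against intent-to-treat bias and is legitimate for that purpose. Survey dropout and session non-completion are different groups.
- A reader might infer that dropout will differ by arm. Section 3.5.1 describes the same surveys, schedule and payments for everyone, section 3.3.2 supplies transport and tablets, and no attrition by arm is given. Different reasons for disengaging are possible but not documented.
- A reader might take 16.5% and 38.1% as the trial's expected error. They are scenarios in one direction, with the true difference exactly at the margin.

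**Conclusion.** The statement in section 3.6.1 is too strong and should be corrected. The model is valid under missing at random with correct specification. With one participant in five expected to be lost, that condition carries real weight, and the one named sensitivity analysis does not test it.

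The size depends on a quantity that the trial cannot observe. Under the simplified assumptions above, a between-arm difference of a quarter to half an SD among dropouts would raise the error at the margin to about three to eight times its nominal 5%, and the reverse would make the test conservative. A trial that observes no difference has more room: about 0.64 SD at 20% missing. This is therefore a reason to examine the assumption, not evidence that a non-inferiority finding would be false. The sample size and the choice of primary model are not in question.

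**What to change.** - Replace the robustness claim with a statement that the model is valid under missing at random, given a correctly specified model.
- Add a delta-adjusted multiple-imputation analysis. Shift the unobserved virtual-arm postpartum scores in the unfavourable direction, in steps, until the upper bound crosses d = 0.25. Report the shift at which this happens and whether it is plausible, in the light of survey missingness in each arm. No fixed pass threshold is needed.
- Include the EPDS scores already extracted from health records as auxiliary variables in the imputation, so that the records inform predictions for people who stop answering surveys.
- Keep the completer analysis, described as an adherence check only.

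The cost is some programming, a few sentences in the analysis plan, and possibly a more cautious conclusion. No new data are required. Section 3.1.2 describes recruitment as ongoing at the time of writing; the change is best fixed before outcomes are compared by arm.

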The Reach Out, Stay strong, Essentials for new mothers (ROSE) program [23] is a well-established interpersonal therapy-oriented group intervention for the prevention of postpartum depression [23,24]. ROSE consists of four 90-min, weekly group sessions and one individual postpartum booster session. Content addresses social support, role transition to motherhood, communication skills, and psychoeducation on postpartum depression [23,27]. Among those identified as being at risk for postpartum depression, ROSE is effective at preventing the onset of postpartum depression [23,24,27,28], with an average reduction in risk of 29 % [29], and effectiveness has been sustained through 12-month follow-up [23]. This clear and abundant evidence led the United States Preventive Services Task Force to name ROSE as one of only two established interventions effective at reducing postpartum depression [29]. Critically, ROSE has demonstrated the benefits of ROSE in preventing postpartum depression in populations that are under-served in mental health treatment, including those living in poverty as well as Black or African-American and Hispanic/Latine individuals [23,24,27,28]. Thus, there is strong evidence supporting ROSE as a postpartum depression prevention program, including among those who face health disparities. Notably, because prior trials have only tested ROSE among people who are identified as at risk for postpartum depression based on prenatal screening [23,24,27,28], implementation of ROSE as universal prevention (i.e., delivered to all pregnant people regardless of risk) remains to be tested.

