## Discussion

4.

Perinatal depression is a highly prevalent complication of pregnancy [1], with higher rates among pregnant individuals who experience contextual stressors such as poverty and racism [11,12]. Perinatal depression not only negatively impacts the pregnant individuals and increases their risk for mortality [3,4], but it also has long-lasting adverse effects on the next generation [5–10]. Therefore, it is important to make effective and culturally sensitive prevention interventions for perinatal depression available for all pregnant individuals and address barriers to care. The current RCT tests the benefits of a novel implementation of ROSE (called La Luz in the current study)—delivering ROSE in a virtual format—which has only demonstrated efficacy when delivered in person. This study has a number of strengths. First, it represents the first effort to provide a novel direct and rigorous test of virtual versus in-person ROSE among socio-demographically high-risk pregnant individuals. Second, it delivers ROSE as universal prevention in a Federally Qualified Health Center through embedding ROSE in a hospital-based obstetric care setting. This universal prevention approach allows ROSE to have greater reach to pregnant individuals who can benefit from this intervention, particularly those who experience greater stigma and barriers to care. Relatedly, because ROSE has only been tested among those who are identified as at risk for post-partum depression based on prenatal screening [23,24,27,28], this study represents a novel test of the effectiveness of ROSE as universal prevention. Moreover, this study provides culturally sensitive care to pregnant individuals in their preferred language, both in-person and virtual intervention modalities, and necessary resources for participating in either modality (e.g., transportation, tablet). In particular, a substantial proportion of the recruited population identify as Hispanic or Latine [54], and many are Spanish-speaking and likely experience linguistic barriers [55]. Delivering ROSE in participants’ preferred language not only represents culturally responsive care but also provides the first empirical test of the effectiveness of ROSE delivered in Spanish. Lastly, the implementation science methods utilized in this research allow us to gain useful knowledge and insight from multiple stakeholders and offer great promise for building effective treatment tools for patients in a sustainable, scalable manner. The resultant stakeholder-informed toolkit of recommendations will support the program’s sustainability in Denver and scalability to other healthcare settings.

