
Alongside these strengths, the study includes design choices that impose some restrictions. For example, we intentionally elected to use a non-inferiority design, which uses two active treatment conditions to empirically test a delivery modality that can increase access to efficacious perinatal depression interventions (i.e., virtual delivery). This was because the literature demonstrates the benefit of ROSE and it would not be ethical to withhold the opportunity to participate. However, this design choice prevents us from testing whether either modality leads to superior clinical outcomes (e.g., lower depression) compared to a control group that does not receive ROSE in either modality. Additionally, although we had the same facilitators for in-person and virtual ROSE to keep facilitator-related factors consistent across conditions, it is possible that any preferences and beliefs facilitators may hold about either modality could inadvertently influence their delivery of ROSE and impact our findings. Lastly, because participants were randomly assigned to either virtual or in-person ROSE, they could not choose their preferred modality. Future research may investigate the effectiveness of ROSE when participants can freely receive their preferred modality, which more closely resembles real-world care.

Despite these restrictions, the current research critically contributes to the knowledge of perinatal depression prevention and addresses care access barriers of underserved populations. If effectiveness of virtual ROSE is demonstrated, the new evidence for a scalable low-cost preventive intervention can be used to reduce perinatal depression and offer accessible treatment options for people who face significant barriers to care. Future research should elucidate mechanisms of change, factors predicting differential impact of intervention, and sustainability and dissemination of virtual ROSE in various healthcare settings (e.g., non-hospital-based clinics).

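### Passing the d = 0.25 non-inferiority test cannot show that virtual, universal or Spanish-language ROSE is effective, although the article says the trial tests this

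*Protocol article*

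**What the plan says.** **The test (section 3.6.1).** The contrast is virtual against in-person delivery on model-based total change in the depression scales, with the "margin of non-inferiority set to an effect size Cohen’s *d* of 0.25". On error rate, "we will use a one-sided test and statistical significance set at" p < .05. On the decision, "Non-inferiority will be shown if the effect size for contrast of total change yields a one-sided" 95% upper bound smaller than +0.25. The rule is purely relative.

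**What is known about the comparator (section 1).** In-person ROSE is described as effective in people at risk, "with an average reduction in risk of 29"%. The same section says that "prior trials have only tested ROSE among people who are identified as at risk for postpartum depression based on prenatal screening" and that "implementation of ROSE as universal prevention (i.e., delivered to all pregnant people regardless of risk) remains to be tested". It adds that the Spanish version exists but that its effectiveness has not been studied.

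**What the trial is said to deliver (section 4 and Abstract).** The Discussion says that "this study represents a novel test of the effectiveness of ROSE as universal prevention", and describes the trial as the first such test of Spanish-language delivery. The Abstract and the end of the Discussion treat the effectiveness of virtual delivery as something this trial may demonstrate and that could then be used for scale-up.

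**What the article concedes (section 4).** Between these statements the Discussion says that "this design choice prevents us from testing whether either modality leads to superior clinical outcomes (e.g., lower depression) compared to a control group" not given ROSE, and gives an ethical reason for having no such group.

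**The concern.** A two-arm non-inferiority trial shows how the new arm compares with the active comparator. To go from there to saying that the new arm works, one must already know that the comparator works in the population enrolled. Here the article says that this is not known for an unselected population or for delivery in Spanish. The concession and the effectiveness statements in the Discussion therefore contradict each other.

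The margin adds a second, weaker worry. If the loss tolerated is of the same order as the whole benefit of in-person ROSE, a pass says little about how much benefit virtual delivery keeps.

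A pass might be read as evidence that a virtual, universal, bilingual programme prevents depression, and used to roll it out to underserved patients, when the design has not tested that.

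**Working it through.** **Step 1. The plan's own sample size.** Section 3.1.1 gives N = 900 with 20% attrition: 900 × 0.80 = 720, or 360 per arm if allocation is 1:1 (assumed). Taking the SD of the contrast as 1 in units of d (equivalent to a baseline-to-end change with correlation 0.5, standardised by the single-visit SD):

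- SE = √(2/360) = 0.0745.
- Power at a true difference of 0 = Φ(0.25/0.0745 − 1.645) = Φ(1.71) = 95.6%.
- N needed after 20% attrition at one-sided 0.05: 495 for 80% power, 688 for 90%, 868 for 95%, 923 for 96%.

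The article states no power, so 900 cannot be strictly reproduced. It is ample for the stated margin, and no arithmetic error is shown.

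**Step 2. What a pass can establish.** The 95.6% depends only on the true difference between the arms. It is the same whether both modalities work equally well or neither works at all. Applied to the three claims:

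| Claim | Comparator needed | In the design? |
|---|---|---|
| ROSE is effective as universal prevention | Unselected people without ROSE | No, both arms receive ROSE |
| ROSE is effective in Spanish | Spanish speakers without ROSE | No, and language follows preference, so it is not randomised |
| Virtual ROSE is effective | No ROSE, or in-person ROSE already proven in this population | No, and section 1 says in-person ROSE is unproven here |

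Change from baseline within an arm does not fill the gap, because symptoms can change through pregnancy and the postpartum year without any intervention. No choice of margin supplies the missing comparator.

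**Step 3. The margin against the only effect figure.** A 29% reduction is a risk ratio of 0.71. Converting it to d needs an untreated rate p0, which the article does not pair with the 29%. Section 1 gives global perinatal rates of 17.0% (major depressive episode) and 27.4% (elevated symptoms). These are used as assumptions, with 40% and 50% added for a population screened as at risk. With p1 = 0.71 × p0:

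- Logit route: d = −ln(OR) × √3/π
- Probit route: d = z(p0) − z(p1)

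| p0 (assumed) | p1 | OR | d, logit / probit | 0.25 as share of d |
|---|---|---|---|---|
| 17.0% | 12.1% | 0.670 | 0.221 / 0.217 | 113% / 115% |
| 27.4% | 19.5% | 0.640 | 0.246 / 0.261 | 102% / 96% |
| 40% | 28.4% | 0.595 | 0.286 / 0.318 | 87% / 79% |
| 50% | 35.5% | 0.550 | 0.329 / 0.372 | 76% / 67% |

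The implied effect is roughly 0.22 to 0.37, and the margin is about 67% to 115% of it.

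**Step 4. How the rule behaves.** A pass needs an observed d below 0.25 − 1.645 × 0.0745 = 0.127. The probability of passing at a true loss δ is Φ((0.127 − δ)/0.0745):

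- δ = 0.125 (half of an effect of 0.25): about 51%.
- δ = 0.22: about 11%.
- δ = 0.26: about 4%.
- If ROSE's effect in an unselected population were only 0.12 (an assumption) and virtual delivery lost all of it: about 54%.

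**The case against.** The strongest reply is that the design is openly relative. The hypothesis in section 2 and the rule in section 3.6.1 speak only of virtual against in-person delivery, the absence of an untreated arm is disclosed and justified, and the closing remark about virtual effectiveness is conditional. This is right about the test, which is not faulted here. It does not rescue the Discussion's statements on universal and Spanish-language effectiveness. The conditional remark still presents as attainable something that the design cannot deliver.

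On the margin the objections carry more weight, and most of them stand:

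- The 29% comes from people at risk, while 17.0% and 27.4% are global rates in pregnant people generally. The article never links them, and it calls its own participants socio-demographically high-risk, so 17% may be too low here.
- The conversion assumes a latent severity scale, whereas the margin applies to total change on the SCL-20 and CESD-10.
- The full protocol may hold a margin rationale. Nothing here rests on its absence.

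From the first two rows of the table in step 3, a reader might infer that the margin swallows the whole benefit of ROSE, so that virtual delivery could lose all of it and still pass. The documents do not support that. At untreated rates of 40% to 50% the margin is about 67% to 87% of the effect. Because the rule acts on the upper bound, a true loss of 0.22 to 0.26 would pass only about 4% to 11% of the time.

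A reader might also want a second test at about half the implied effect, d of about 0.12, before saying that benefit is preserved. That figure inherits the same assumptions. Its power on a change contrast is only about 49% (Φ(0.12/0.0745 − 1.645)). Passing it would still not show that there was any benefit to preserve.

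**Conclusion.** The effectiveness statements are wrong as written. Meeting the d = 0.25 rule cannot establish that virtual, universal or Spanish-language ROSE is effective, because both arms receive ROSE and the article itself says that ROSE is untested in the last two settings. This needs no calculation and holds at any margin.

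The size of the margin is a caution, not a proven error. Against the only effect figure given, 0.25 is about 67% to 115% of the implied benefit. That range rests on assumed untreated rates of 17% to 50%, a latent-scale conversion, and a point estimate from people at risk. A smaller effect in an unselected population would raise the share. An upper bound well below 0.25 would say more about virtual against in-person delivery, but still nothing about either against no ROSE.

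**What to change.** 1. State the conclusion of a positive test as: virtual delivery is not worse than in-person delivery by 0.25 SD or more.
2. Remove or reword, in the plan and in the eventual report, the statements that the trial tests or may demonstrate the effectiveness of ROSE as universal prevention, in Spanish, or virtually. For universal and Spanish-language use, the trial can describe delivery, implementation and the relative performance of the two modalities.
3. Report the estimate and its one-sided 95% upper bound beside the implied ROSE effect range (about 0.22 to 0.37, with its assumptions stated), so that readers can see how much benefit could have been lost.

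This takes no extra patients, no alpha, and no change to the test or margin. Section 3.1.2 describes recruitment as ongoing, so the wording can be settled before results are known. The cost is a less favourable claim.
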